### Data management and quality assurance

2.7

All data will be managed in accordance with institutional and international standards for research involving human participants. Each child will be assigned a unique identification code, and all data will be labeled with this code rather than personal identifiers to protect confidentiality. Video files of TGMD-3 performances and EEG recordings will be stored on encrypted, password-protected hard drives accessible only to the research team. Questionnaire data will be entered into a secure database.

TGMD-3 scoring will be completed by two independent raters who are blinded to both group allocation and time point. Inter-rater reliability will be assessed using intraclass correlation coefficients, and any discrepancies will be resolved by consensus discussion. EEG data will be preprocessed using standardized pipelines to minimize noise and artifact, including filtering, segmentation, and removal of movement-related or ocular artifacts. Preprocessing will be performed by trained staff who are blinded to group allocation.

A designated data manager will oversee double-entry checks for questionnaire and TGMD-3 scoring data to ensure accuracy. Any irregularities will be flagged and corrected in consultation with the principal investigator. Interim analyses will not be conducted, but descriptive monitoring of recruitment, retention, and fidelity will be used to ensure study progress.

### Statistical analysis

2.8

All analyses will follow the intention-to-treat principle, with all children analyzed according to their randomized class regardless of adherence or attendance. Descriptive statistics will be reported for baseline demographic and developmental characteristics, including age, sex, height, weight, and baseline TGMD-3 scores, to assess comparability between groups. Continuous variables will be summarized using means and standard deviations, while categorical variables will be summarized using frequencies and percentages.

For the primary outcome of gross motor competence, linear mixed-effects models will be used to examine group (intervention vs. control) by time (baseline vs. post-intervention) interactions, accounting for clustering at the class level. Models will include random intercepts for class and child, and fixed effects for group, time, and the group-by-time interaction. Relevant covariates, including age and sex, will be included where appropriate. Because the number of clusters (classes) in the present study is relatively small, degrees of freedom for fixed effects will be estimated using the Satterthwaite approximation within the linear mixed-effects modeling framework. This approach reduces potential underestimation of standard errors and helps control Type-I error rates in studies with limited cluster numbers.

For EEG outcomes, analyses will follow the pre-specified hierarchy of neural endpoints. The primary EEG analysis will focus on frontal theta power during resting state. A secondary task-related neural index will be the N2 amplitude elicited during the Go/No-Go task. Separate linear mixed-effects models will be constructed for each neural endpoint to evaluate group-by-time interactions, using the same clustering structure as described for the primary motor outcome (random intercepts for class and child).

Additional EEG measures will include spectral power indices in the alpha and beta frequency bands, which will be analyzed using similar mixed-effects models. To account for multiple comparisons across these secondary neural measures, false discovery rate adjustments will be applied. These analyses will be interpreted as supportive and contextual rather than confirmatory.

Exploratory analyses will examine associations between changes in TGMD-3 scores and changes in EEG-derived neural indicators, as well as feasibility analyses of EEG recordings obtained during selected motor tasks. Correlational analyses will use Pearson or Spearman coefficients as appropriate, with regression models applied to adjust for relevant covariates. Results from exploratory analyses will be interpreted as hypothesis-generating.

Behavioral performance measures from cognitive tasks, including accuracy and reaction time, will be analyzed using mixed-effects models parallel to those used for neural indices. Questionnaire outcomes (BRIEF-P and SDQ) will also be examined using mixed-effects models to compare baseline-to-post changes across groups, adjusting for clustering.

Missing data for behavioral and questionnaire outcomes will be handled using maximum likelihood estimation within the linear mixed-effects modeling framework, which provides unbiased parameter estimates under the assumption of missing at random (MAR). This will serve as the primary approach to incomplete outcome data. The proportion and pattern of missingness will be examined descriptively. If missingness exceeds anticipated levels or suggests deviation from the MAR assumption, sensitivity analyses will be conducted to evaluate the robustness of findings.

All statistical tests will use a two-sided alpha level of 0.05. Analyses will be performed using SPSS 25.0 (IBM, Armonk, NY, USA).

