### Sample size

2.3

The sample size was calculated to detect meaningful differences in gross motor competence between the intervention and control groups, while accounting for the cluster-randomized design. Previous intervention trials and meta-analyses of preschool motor-skill programs have consistently reported large effect sizes, often exceeding 1.0, for improvements in fundamental motor skills (7). Based on this evidence, we adopted an assumption of an effect size of 1.0 for between-group differences.

Using a two-tailed alpha of 0.05 and a statistical power of 80%, an individually randomized design would require approximately 21 children per group. Because this study uses class-level randomization, the required sample size was adjusted for clustering. Assuming an average class size of 25 and an intra-class correlation coefficient of 0.05, the design effect is estimated at 2.2. This adjustment results in an effective sample size of 46 children per group, or 92 children in total. To accommodate an anticipated dropout rate of 15%, we plan to recruit approximately 110 children overall, distributed across four to six kindergarten classes in Changsha city.

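### The primary group-by-time model has no random term for class differences in gain, so its test is essentially unclustered, and the Satterthwaite degrees of freedom do not correct this

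*Protocol article*

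**What the plan says.** All references are to the protocol article.

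- **Contrast.** Statistical analysis (2.8) states that "linear mixed-effects models will be used to examine group (intervention vs. control) by time (baseline vs. post-intervention) interactions, accounting for clustering at the class level". Study design (2.1) fixes the two time points at week 0 and week 16.
- **Model terms.** The next sentence in 2.8 lists them: "Models will include random intercepts for class and child, and fixed effects for group, time, and the group-by-time interaction". Age and sex may be added as covariates.
- **Small number of classes.** "degrees of freedom for fixed effects will be estimated using the Satterthwaite approximation within the linear mixed-effects modeling framework". The article then claims: "This approach reduces potential underestimation of standard errors and helps control Type-I error rates in studies with limited cluster numbers".
- **Other outcomes.** The EEG models are fitted "using the same clustering structure as described for the primary motor outcome (random intercepts for class and child". The Go/No-Go behavioural models are described as parallel to the EEG models. The questionnaire models are said only to adjust for clustering.
- **Sample size (2.3).** "Because this study uses class-level randomization, the required sample size was adjusted for clustering", with class size 25, ICC 0.05 and design effect 2.2. About 110 children in four to six classes are planned.
- **Test level.** "All statistical tests will use a two-sided alpha level of 0.05".

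**The concern.** Classes are randomized, so the standard error of the treatment effect must reflect how much classes differ in the quantity being compared. Here that quantity is gain from baseline to week 16. A class intercept describes how classes differ in level at both times; it says nothing about how they differ in gain. The programme is taught by regular kindergarten teachers for 16 weeks, and delivery is expected to vary enough to justify biweekly fidelity scoring and feedback (Intervention, 2.5). Some class variation in gain is therefore plausible, and no random term in the model can absorb it.

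At stake is the primary TGMD-3 test. Differences between classes that have nothing to do with the programme would count as evidence for it, and the confidence interval would be too narrow. The sample size section inflates for clustering in the between-group difference, while the analysis tests that difference as if there were none.

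**Working it through.** **1. The plan's own figures.** Design effect: 1 + (25 − 1) × 0.05 = 2.2. Then 21 × 2.2 = 46.2, taken as 46 per group and 92 in total; 92 / 0.85 = 108.2, rounded to about 110. These steps reproduce. The starting figure does not: "Using a two-tailed alpha of 0.05 and a statistical power of 80%, an individually randomized design would require approximately 21 children per group", yet an effect size of 1.0 needs 17 per group by the t-test. That error is conservative and is a separate matter. What counts here is that the plan puts clustering into the variance of the group difference.

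**2. Cancellation.** For child i in class j at time t, the model is

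y(ijt) = fixed effects + u(j) + v(ij) + e(ijt).

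The change score is y(ij1) − y(ij0) = fixed time effects + e(ij1) − e(ij0). Both u(j) and v(ij) are gone. With complete data the interaction estimate is the difference in mean change, and its standard error is that of a pooled t-test on children with N − 2 degrees of freedom: 108 for 110 children, 90 for 92. The number of classes minus 2 is 2 to 4.

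Fitted models confirm this. In a complete simulated data set (four classes of 25), the mixed-model standard error was 0.18152 and the unclustered change-score standard error was 0.18152. With 15% of post-tests missing, the two were 0.1505 and 0.1518.

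**3. Type I error.** Let ρ be the ICC of change and m the class size. The true variance of the contrast exceeds the modelled one by about DE = 1 + (m − 1)ρ, so

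true type I error ≈ P(|T| > t_crit / √DE).

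Example: 110 children in four classes gives m = 27.5. With ρ = 0.05, DE = 1 + 26.5 × 0.05 = 2.325 and √DE = 1.525. Then 1.982 / 1.525 = 1.30, and P(|T| > 1.30) = 19.6%.

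| Children, classes | ρ = 0 | 0.02 | 0.05 | 0.10 |
|---|---|---|---|---|
| 110, four | 5.0% | 11.2% | 19.6% | 30.2% |
| 110, six | 5.0% | 9.0% | 15.0% | 23.3% |
| 92, four | 5.0% | 10.1% | 17.4% | 27.0% |
| 92, six | 5.0% | 8.3% | 13.3% | 20.6% |

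Simulation (20,000 trials per setting) agrees. For four classes of 27 it gave 19.6% at ρ = 0.05 and 31.3% at 0.10; for six of 18 it gave 15.2% and 23.8%. A t-test on class-mean changes stayed at 4.6–5.2% throughout.

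**4. How ρ relates to the stated 0.05.** If 0.05 is the ICC at each time point, the ICC of change depends on two unstated quantities: the correlation c of the class effect between the two times, and the within-class child correlation r:

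ρ = 0.05(1 − c) / [0.05(1 − c) + 0.95(1 − r)].

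For c = 0.9 and r = 0.7, ρ = 0.005 / (0.005 + 0.285) = 0.017. Over r = 0.5–0.8 with 110 children, type I error is 7–13% for c = 0.9, 9–20% for c = 0.8 and 15–33% for c = 0.5. For c = 1 it is 5%.

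**5. Power of a class-level test.** Take d = 1.0 in SD units of change and ρ = 0.05. Four classes of 27: DE = 2.3, SE = √(4 × 2.3 / 108) = 0.292, noncentrality 1 / 0.292 = 3.43 on 2 degrees of freedom; simulated power 46%. Six classes of 18: DE = 1.85, SE = √(4 × 1.85 / 108) = 0.262, noncentrality 3.82 on 4 degrees of freedom; simulated power 81%. With about 92 children the figures are 44% and 78%.

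**The case against.** **The size is not fixed by the documents.** This is the strongest point, and it stands. A reader might infer that the type I error simply is 15–20%. That needs an ICC of change of 0.05, and the article does not label its 0.05 as such. Class effects that are stable over time cancel legitimately. If they were perfectly stable, the planned test would hold 5%. The manuals, training and fidelity feedback also aim to limit variation in delivery in the intervention arm. The inflation must therefore be given as a conditional range.

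**The cause is not fully documented.** A reader might picture a single teacher per class driving its gains. The Intervention section refers only to regular kindergarten teachers and says staff do not rotate between arms. The point does not need more than that.

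**The reach is limited.** A reader might extend the defect to every outcome. The EEG models copy the structure explicitly and the Go/No-Go models are called parallel, but no random effects are given for BRIEF-P and SDQ. The Discussion also declares the EEG analyses exploratory, so the consequence is gravest for TGMD-3.

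**Cancellation is exact only with complete data.** True, and 15% dropout is anticipated. The fits with 15% missing show that the standard errors remain close.

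**The detail might be left to an analysis plan.** This does not stand. The article lists the random effects, names the degrees-of-freedom method and asserts that it controls type I error. That is a stated choice. The general phrase about class clustering cannot imply a class-by-time term when the next sentence lists the terms and the EEG paragraph repeats them.

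**Conclusion.** The concern holds in a conditional form. As specified, the primary test leaves class-level variation in gain out of its standard error, and it uses child-level degrees of freedom. The article's sentence on Satterthwaite is wrong for this contrast: the method does not change the standard error, and here it returns about N − 2.

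The structural defect follows from the stated model and needs no numerical assumption. Its size depends on the ICC of change, which is not given: about 13–20% type I error at 0.05, about 8–11% at 0.02, about 21–31% at 0.10, and 5% at zero. These figures assume four or six equal classes and 92–110 children. A stronger reading, that inflation to a particular level is certain, is not supported. Because this is the primary test and the plan's own design effect presumes clustering in the group difference, the text should be corrected before analysis.

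**What to change.** Make the primary test a class-level comparison: a t-test with (number of classes − 2) degrees of freedom, either on class-mean change in TGMD-3 or on class means of week-16 TGMD-3 adjusted for baseline TGMD-3, age and sex.

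Alternatively, keep the repeated-measures model, add a class-by-time random effect, and refer the group-by-time effect to (number of classes − 2) degrees of freedom. This retains the planned likelihood handling of incomplete data but is conservative when the class variance is estimated as zero. With random class variation in gain fitted by REML and those degrees of freedom, simulated type I error at ICC 0.05 was about 0.2% with four classes and 2.0% with six.

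Use the same structure for the EEG and Go/No-Go models, and state the structure for the questionnaires. Delete or correct the sentence claiming that Satterthwaite reduces underestimation of standard errors.

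No new data are needed, but the cost is more than wording. Intervals widen, and power falls to about 45% with four classes and about 80% with six, if d = 1.0 is in SD units of change and the ICC of change is 0.05. Sample size (2.3) should fix the number of classes and restate its 80% power for that number.

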### Randomization and blinding

2.4

Randomization will be performed at the class level. After baseline assessments are completed, participating classes will be randomly assigned in a 1:1 ratio to either the intervention group (motor-focused physical education) or the control group (ordinary physical education). The allocation sequence will be generated by an independent researcher using a computer-based random number generator and will not be disclosed to the assessment team until all baseline testing has concluded.

Due to the nature of the intervention, it is not possible to blind teachers or participants to group allocation. However, outcome assessors will remain blinded throughout the study. Specifically, individuals conducting the motor skill assessments and EEG recordings will not be informed of class assignments. To further reduce bias, video recordings of motor skill performances will be scored by two independent raters who are blinded to intervention status and assessment time point. Data analysts will also be blinded to group labels until the primary analyses are completed.

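### The primary group-by-time model is a change-score comparison that uses baseline TGMD-3 inefficiently, leaves age and sex main effects almost without influence, and omits class-level variation in change from its standard error

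*Protocol article*

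**What the plan says.** Section 2.8 of the protocol article tests the primary outcome through the group-by-time term of a linear mixed model with two time points. The terms are fixed: "Models will include random intercepts for class and child, and fixed effects for group, time, and the group-by-time interaction". The group main effect leaves the arms' baseline means free to differ. Covariates get one sentence: "Relevant covariates, including age and sex, will be included where appropriate". No covariate-by-time term and no class-by-time random effect is mentioned. Apart from being one of the two outcome measurements, baseline TGMD-3 serves only to describe comparability of the groups.

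Section 2.4 places baseline before allocation: "After baseline assessments are completed, participating classes will be randomly assigned in a 1:1 ratio". Section 2.3 supplies the clustering figures: "Assuming an average class size of 25 and an intra-class correlation coefficient of 0.05, the design effect is estimated at 2.2", and "we plan to recruit approximately 110 children overall, distributed across four to six kindergarten classes in Changsha city". Incomplete behavioral and questionnaire outcomes are handled by maximum likelihood under MAR (section 2.8). The EEG models use the same clustering structure, and the task and questionnaire outcomes also get mixed models of baseline-to-post change.

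**The concern.** A two-wave model with free arm baselines and intercept-only random effects estimates a difference in change. Whatever is constant within a child over time drops out of that difference. This covers the child intercept, which is intended, but also age, sex and the class intercept.

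With only two or three classes per arm and children aged 4 to 6, a chance age difference between arms is plausible. The report could call the result adjusted for age and sex although the adjustment barely touched it. The model is also presented as accounting for class clustering, while the term being tested carries no class-level variance. Finally, it spends precision on estimating a baseline difference whose expectation is zero under randomization.

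**Working it through.** **Inputs from the documents.** ICC 0.05, effect size 1.0, 92 children before and about 110 after the dropout allowance, four to six classes (section 2.3). Class sizes used: 23 and 27 with four classes (92/4 = 23; 110/4 = 27.5), 16 and 18 with six (92/6 = 15.3; 110/6 = 18.3).

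**Assumed, because not stated.** Child-level baseline–post correlation *c* = 0.3–0.7; class-level correlation *k* = 0.5–1; equal variances at both times, scaled to 1.

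**The plan's own figures.** The plan states no standard error or baseline–post correlation. Its sample-size chain reproduces from 21 per group onward: 1 + 24 × 0.05 = 2.2; 21 × 2.2 = 46.2; 92/0.85 = 108.2, so about 110. The 21 itself does not follow from an effect of 1.0 at 80% power, which needs 16 (normal) or 17 (*t*) per group; 21 gives 88.5%. That is a separate, conservative discrepancy and nothing below depends on it.

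**1. What the interaction estimates.** REML fits to simulated trials (four classes of 23, ten data sets per setting, age and sex predictive of the score):
- Complete data: the interaction with covariates, without them, and the simple difference in mean change all agreed. In one example each gave 1.3445 (SE 0.2237); with and without covariates the difference was 0.0000 in every data set.
- 15% of post scores missing: adding age and sex moved the estimate by at most 0.018 SD and the SE by at most 0.0034.

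**2. Gain from a common baseline.** For a class mean based on *m* children, *V* = 0.05 + 0.95/*m* is the variance at each time, *C* = 0.05*k* + 0.95*c*/*m* the covariance, and *r* = *C*/*V*. The free-baseline contrast has variance proportional to 2*V*(1 − *r*); the common-baseline contrast, *V*(1 − *r*²). The SE ratio is √[(1 + *r*)/2].
- Smallest gain (*m* = 27, *c* = 0.7, *k* = 1): *V* = 0.0852, *C* = 0.0746, *r* = 0.876, ratio 0.969, a 3% smaller SE.
- Largest gain (*m* = 16, *c* = 0.3, *k* = 0.5): *V* = 0.1094, *C* = 0.0428, *r* = 0.391, ratio 0.834, a 17% smaller SE.
- The complete-data simulations fall inside this range: mean SE 0.2125 to 0.1958 (8%) at overall correlation 0.5, and 0.1646 to 0.1572 (4%) at 0.7.

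**3. Age imbalance.** If arms differ by 0.4 year and change depends on age by 0.1–0.3 SD per year (both assumed), 0.4 × 0.1 = 0.04 to 0.4 × 0.3 = 0.12 SD stays in the estimate. An age main effect does not remove it; an age-by-time term can.

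**4. Class-level variation in change.** The true variance of a class's mean change is 2 × 0.05(1 − *k*) + 2 × 0.95(1 − *c*)/*m*. The stated model carries essentially only the second part, and in the complete-data fits its SE equalled the unclustered change-score SE. The understatement factor is √[1 + *m* × 0.05(1 − *k*)/(0.95(1 − *c*))].
- *m* = 16, *c* = 0.3, *k* = 0.9: √(1 + 0.08/0.665) = 1.06.
- *m* = 27, *c* = 0.7, *k* = 0.8: √(1 + 0.27/0.285) = 1.40.
- *k* = 1: exactly 1, so no understatement.

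Satterthwaite degrees of freedom do not repair this: they set the reference distribution and add no missing variance component.

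**5. Post-score ANCOVA for comparison.** With a child-level baseline covariate (coefficient about *c*) and a random class intercept, the variance is proportional to *V*(1 + *c*²) − 2*cC*.
- *m* = 27, *c* = 0.3, *k* = 1: 0.0852 × 1.09 − 0.6 × 0.0606 = 0.0565, against 2(*V* − *C*) = 0.0493 for change; SE ratio 1.07.
- *m* = 16, *c* = 0.3, *k* = 0.5: 0.1094 × 1.09 − 0.6 × 0.0428 = 0.0935, against 0.1332; SE ratio 0.84.

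So it ranges from about 16% more precise to 7% less precise than the change-score contrast.

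**The case against.** Group-by-time is a standard, valid analysis of a two-wave trial and matches the hypothesis of greater improvement; choosing another form is partly a matter of efficiency. That stands, but it does not answer the missing class-level variance or the ineffective covariates.

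The covariate sentence neither states nor excludes interactions with time, and a fuller analysis plan may settle this. Main effects only is therefore the natural reading, not the literal text. The room left by the covariate wording is also partly limited because analysts stay blinded to group labels until the primary analyses are complete (section 2.4).

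Four stronger readings are tempting, and the documents do not support them:
- That baseline is thrown away. It is in the model as an outcome, and above a baseline–post correlation of 0.5 the change contrast beats a post-only comparison at child level.
- That covariate adjustment does nothing at all. This is exact only with complete data; under maximum likelihood with the expected 15% dropout the covariates have a small effect and can support MAR.
- That the age gap is bias. It is chance imbalance under assumed inputs, averages to zero over randomizations, and is small beside the planned effect of 1.0.
- That variance would fall by 35%, 25% or 15% (correlation 0.3, 0.5, 0.7). Those savings come from a child-level formula. A change score already removes stable class differences, so they do not carry over to four to six classes.

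**Conclusion.** The point holds in a bounded form and should be corrected. With complete data the stated primary analysis is a difference in mean change, whatever age and sex main effects or class intercept accompany it.

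- **Precision:** a common-baseline model has a 3–17% smaller SE, given ICC 0.05, four to six classes and the assumed correlations.
- **Covariates:** read as main effects, age and sex cancel with complete data and are negligible with about 15% missing post scores. This is a matter of chance imbalance and of how the adjustment would be described.
- **Clustering:** this is the most consequential part. If class effects correlate 0.8–0.9 over time, the reported SE is too small by a factor of about 1.06–1.4; if they are perfectly stable, it is not understated. The documents give no figure for this correlation.

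A reader might infer that post-score ANCOVA is an equivalent remedy. It is not: with four classes and stable class effects it can be up to about 7% less precise than the change-score contrast.

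**What to change.** Reword section 2.8 so that the primary analysis is a longitudinal mixed model with:
- a common baseline mean across arms, with the treatment effect as the arm difference at post-test;
- random effects for class, class-by-time and child;
- age, sex, age-by-time and sex-by-time always included, replacing the conditional covariate wording;
- REML estimation with Satterthwaite degrees of freedom.

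This keeps children with a missing post score, as the missing-data paragraph intends. Use the same form for the EEG, task and questionnaire outcomes. Post-score ANCOVA on baseline, age and sex with a random class intercept is a simpler alternative, provided its possible loss of precision with four classes is accepted.

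The cost is a text change: baseline TGMD-3, age and sex are already collected. The drawback is real. With four to six classes the class-by-time variance is poorly estimated and the degrees of freedom are few, so the reported interval may be wider. It will describe the uncertainty of a class-randomized comparison more honestly.

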Therefore, the objective of the present trial is to evaluate the effects of a semester-long motor-focused physical education program on gross motor competence and exploratory neurodevelopmental indicators in preschool children. Based on existing behavioral and developmental neuroscience literature, we hypothesize that children receiving the motor-focused intervention will demonstrate greater improvements in gross motor competence than those in the control condition, exhibit changes in pre-specified electroencephalography (EEG) indices associated with inhibitory control and attentional regulation, and show positive associations between gains in motor competence and changes in functional neural indicators. By integrating standardized behavioral assessment with non-invasive measures of functional brain activity within real-world kindergarten settings, this study aims to clarify whether structured motor enrichment is accompanied by concurrent neurodevelopmental correlates during a sensitive developmental window.

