Several limitations warrant consideration. First, although portable EEG enables assessment in preschool environments, recordings are inherently vulnerable to movement artifacts and compliance challenges. Despite standardized preprocessing and artifact rejection procedures, some data loss is anticipated. Second, while the study is powered to detect large effects on the primary behavioral outcome, it is not powered for definitive inference regarding neurophysiological endpoints. Accordingly, EEG analyses should be interpreted as exploratory and hypothesis-generating. Third, the intervention duration is limited to one academic semester within a single regional context, and longer-term developmental trajectories cannot be inferred from the present protocol.

Despite these limitations, this study has the potential to make several important contributions. It will provide one of the first randomized controlled trials to integrate EEG into the evaluation of early motor-focused physical education, thereby linking behavioral and neural outcomes in a developmental framework. It will also generate practical insights for educators and policymakers by identifying not only whether motor-focused programs are beneficial, but also how they exert their influence on the developing brain. Ultimately, this knowledge may inform the design of optimized physical education curricula that promote both motor competence and cognitive readiness in young children, with long-term implications for academic achievement, physical activity participation, and health across the lifespan.

Within these boundaries, the study aims to contribute incremental evidence to the growing literature linking motor development and neurocognitive functioning in early childhood. The findings are intended to clarify whether structured motor-focused programs are associated with concurrent functional neural indicators during a sensitive developmental period. If such associations are observed, they may inform future research examining scalable approaches to support early developmental trajectories within educational settings.

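### The motor-EEG association is planned as correlations of change scores without requiring arm or class, so a pooled coefficient can partly restate the two treatment effects

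*Protocol article*

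**What the plan says.** The Introduction hypothesizes, alongside the effects on motor competence and on EEG, that children will "show positive associations between gains in motor competence and changes in functional neural indicators".

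Statistical analysis (2.8) covers this under exploratory work: "Exploratory analyses will examine associations between changes in TGMD-3 scores and changes in EEG-derived neural indicators". The method is: "Correlational analyses will use Pearson or Spearman coefficients as appropriate, with regression models applied to adjust for relevant covariates". The status is also given: "Results from exploratory analyses will be interpreted as hypothesis-generating".

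The covariates for the association are not listed. The only ones named in 2.8 belong to the primary model: "Relevant covariates, including age and sex, will be included where appropriate". The models for the other outcomes do address clustering. The EEG endpoints are modelled "using the same clustering structure as described for the primary motor outcome (random intercepts for class and child", the alpha and beta measures and the Go/No-Go behavior get similar or parallel mixed models, and the questionnaire models are stated to adjust for clustering. The association analysis mentions neither class nor arm.

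Outcomes (2.6) and the Discussion (3) say that the EEG work is not meant to settle mechanism. Later in the Discussion, the trial is nevertheless said to identify not only whether programs help, "but also how they exert their influence on the developing brain".

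**The concern.** The first two hypotheses predict that the program moves TGMD-3 and changes EEG. If both happen, treated children sit apart from control children on both axes, and a correlation over all children picks up that separation. The third hypothesis would then partly repeat the first two instead of adding information about whether children who gain more in motor skill also change more in EEG.

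Class raises a smaller problem of the same kind. Children in one class share a teacher and setting, so with four to six classes, chance class-level differences in both outcomes can look like an association if children are treated as independent.

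An analyst could report a pooled coefficient and comply fully with the text. A reader could then take it as evidence of motor-neural coupling, which the Discussion's sentence on how programs act would encourage.

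**Working it through.** **The plan's own figure.** The protocol gives none for the association analysis, so there is nothing to reproduce.

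**Inputs**
- Motor effect d1 = 1.0, from Sample size (2.3): "we adopted an assumption of an effect size of 1.0 for between-group differences". It is taken here as SDs of change, which the protocol does not specify.
- n = 92 (46 per group), four to six classes, ICC 0.05: Sample size (2.3). Allocation 1:1: Randomization and blinding (2.4).
- EEG effect d2: not in the protocol. Range assumed: 0.2 to 1.0 SD of change.
- ICC of the change scores: not in the protocol. The planning value of 0.05 is borrowed.
- Within-arm correlation: set to zero.

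**Step 1: induced correlation.** With 1:1 arms the arm indicator has variance 1/4. The pooled covariance is therefore d1·d2/4, and the pooled variances are 1 + d1²/4 and 1 + d2²/4:

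r = (d1·d2/4) / √[(1 + d1²/4)(1 + d2²/4)]

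For d1 = 1.0 and d2 = 0.5: 0.125 / √(1.25 × 1.0625) = 0.125 / 1.152 = 0.108.

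**Step 2: rejection at nominal two-sided 5%.** By Fisher's z, atanh(r)·√(n − 3) is compared with ±1.96, and √89 = 9.43. For r = 0.108 the mean of z is about 1.03, so the chance of falling outside ±1.96 is about 18%.

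| Assumed EEG effect (SD) | Induced r | Rejection, n = 92 |
|---|---|---|
| 0 | 0 | 5% |
| 0.2 | 0.044 | about 7% |
| 0.3 | 0.066 | about 10% |
| 0.5 | 0.108 | 18% |
| 0.8 | 0.166 | 35% |
| 1.0 | 0.200 | 48% |

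If the EEG index falls in the treated arm, r has the same size with a negative sign. Varying d1 from 0.5 to 1.5 at d2 = 0.5 moves r from 0.059 to 0.146.

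**Step 3: add class, then adjust.** Simulation with 3,000 runs per cell, d1 = 1.0, n = 92, four classes, ICC 0.05, independent class effects on the two outcomes and no within-arm link:

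| EEG effect (SD) | Pearson, pooled | Arm in model | Class fixed effects |
|---|---|---|---|
| 0 | 7.5% | 5.5% | 4.8% |
| 0.3 | 12.2% | 4.9% | 4.7% |
| 0.5 | 21.6% | 5.6% | 5.1% |
| 1.0 | 49.6% | 5.4% | 5.3% |

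Spearman behaves like Pearson (7.4%, 12.7%, 22.0%, 49.8%). With no EEG effect, pooled Pearson rejects in 7.0% with six classes, and in 11.7% with four classes if the ICC is 0.10. Arm is the larger source of distortion and class the smaller.

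**The case against.** The strongest reply is that the text is silent and does not say that arm and class are left out. The same sentence that names the coefficients adds regression for relevant covariates, and age and sex are given elsewhere in 2.8 as examples only. Arm could be among them, and a fuller plan could say so. This stands for the regression. It does not help the coefficients, which the protocol has already chosen and which cannot hold either term.

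Second, the Introduction speaks of associations without limiting them to within arms. If the program shifts both outcomes, the pooled correlation is truly non-zero, so the rejection rates above are error rates only for the within-arm association. That is correct. But the pooled quantity then adds little to the two treatment comparisons, and the reader cannot separate the parts.

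Third, the size rests on assumed EEG effects. The protocol says that it is not powered for EEG and expects some data loss. Modest effects give r of only 0.04 to 0.07, and fewer usable recordings would lower the rejection rates, though not the induced r.

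Fourth, the protocol repeatedly labels this work exploratory. That limits the harm, but the label concerns strength of evidence and does not change which quantity is estimated.

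**Conclusion.** The point holds in a limited form. The protocol names an estimator for a listed hypothesis that cannot separate within-arm association from the joint treatment effect, and does not require arm or class in the accompanying regression. The induced r is about 0.04 to 0.20 for assumed EEG effects of 0.2 to 1.0 SD, with rejection of about 7% to 48% at n = 92. Class clustering alone gives about 7.5% under the assumed ICC of 0.05 and four classes. These figures assume a motor effect of 1.0 SD of change, no within-arm association and usable EEG at both times for all 92 children.

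A reader might infer that the plan deliberately ignores arm and class, or that a false positive correlation is to be expected. The documents support neither. The covariates are left open, and the Introduction predicts EEG changes without a direction, so the artefact could be negative. The upper end of the range needs an EEG effect as large as the assumed motor effect. The primary outcome is not affected.

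**What to change.** In 2.8, make the main association analysis a regression of EEG change on TGMD-3 change with group as a required term and class accounted for, by a random intercept or by class fixed effects. Because whole classes are randomized, class fixed effects already absorb the group term. Report the within-arm slope with its interval, and keep any pooled Pearson or Spearman coefficient as descriptive only. Baseline values and a group-by-TGMD-3-change term are optional.

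In the Discussion, bring the phrase "but also how they exert their influence on the developing brain" into line with 2.6 and with the Discussion's own statement that the EEG measures complement the behavioral findings and do not establish mechanism.

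The cost is wording and a few degrees of freedom in an exploratory model: one for group with a random class intercept, or three to five for fixed effects with four to six classes. No new data or participants are needed.
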